### Intervention methods

#### Group Intervention 1: Walking and a meaningful conversation

*Objective*: The primary objective of this intervention will be to promote physical activity and social interaction through nature-based walks, followed by meaningful conversation sessions. Engaging in outdoor activities and sharing personal experiences will aim to strengthen emotional connections and enhance mental health.*Setting*: The intervention will take place in a safe, accessible, and natural setting in a large park in Khafr County. The setting will be chosen to create a relaxing and enjoyable environment for walking and conversation.*Session structure*: *Warm-up (10 minutes)*:Prior to the main exercise, the participants will complete a 10-minute warm-up consisting of light walking (3–5 min) followed by dynamic stretches to gradually increase heart rate and prepare the musculoskeletal system. Movements will be performed in a controlled manner through a full range of motion.*Walking activity (50 minutes)*:The participants will perform a 50-minute moderate-paced walk (approximately 3-4 km/h) in the park. During the walk, trained researchers will provide real-time supervision to ensure participant safety and protocol adherence. The monitoring team will visually assess exertion levels and observe for any signs of gait instability or physical distress. Particular attention will be given to environmental factors such as terrain variations and weather conditions that might affect walking performance. The protocol will allow for immediate pace adjustments, brief rest periods if needed, or session termination if participants show signs of excessive fatigue. Staff will carry basic medical supplies throughout all walking sessions.*Cool-down and Discussion (10 minutes)*:Post-exercise, the participants will engage in 10 minutes of slow walking and static stretching (15–30 seconds per muscle group) to safely return to baseline physiological states. All sessions will be supervised for proper execution.*Meaningful Conversation (50 minutes)*:After the walking session, while enjoying a brief reception, participants will engage in guided conversations focusing on positive emotions, personal stories, and life reflections. A series of open-ended questions will be used to stimulate discussion, such as:What is a memorable moment from childhood?What are your favorite natural memories?

The researcher will act as a facilitator and will ensure that all participants feel comfortable and are encouraged to actively share their experiences. The session will end with a brief discussion of the day’s activities. Positive experiences shared during the conversations will be reinforced by the researcher.

#### Group 2: Nature-based meditation

*Objective*: The nature-based meditation intervention will aim to increase mental calmness and cognitive empowerment.*Setting*: Similar to the first group, participants in this intervention will be taken to the same park where a quiet, distraction-free environment will be created for the meditation sessions.*Session structure*: The meditation in this study will be designed based on evidence-based mindfulness techniques, ensuring its suitability for older adults. The sessions will be held in a controlled and supervised environment, ensuring that the techniques are adapted to the physical and cognitive capacities of older adults. Participants will be offered modifications to accommodate varying levels of comfort and posture adjustments to enhance their overall experience. Sessions will be led by a qualified clinical psychologist with experience working with older adults, who will provide a structured and guided approach to increasing relaxation, emotional regulation, and cognitive focus. Each session will follow a standard structure consisting of the following three steps:A*Introduction and breathing exercises (10 min)*: The session will begin with a brief introduction to the principles of meditation, emphasizing the importance of breathing regulation as a foundational practice. The participants will be guided through diaphragmatic breathing exercises to promote relaxation and enhance oxygenation. Techniques such as paced breathing (e.g., inhaling for four counts, exhaling for six counts) will be introduced to regulate the heart rate and induce a state of calm. This will help participants mentally prepare for meditation.B*Guided meditation (60 min)*: The core meditation practice will incorporate multiple scientifically validated techniques to optimize mental clarity and emotional stability:*Mindfulness meditation*: Participants will be guided to cultivate present-moment awareness by observing their thoughts and emotions without judgment. Sensory awareness exercises, including attention to bodily sensations, ambient sounds, and breath rhythm, will be conducted to improve cognitive focus.*Body scan meditation*: A systematic approach will be employed, in which participants will direct their awareness progressively through different parts of the body, identifying and releasing areas of tension. This technique will facilitate physical relaxation and enhance somatic awareness.*Guided imagery*: To strengthen relaxation responses, participants will visualize calming natural environments, such as forests, oceans, or meadows. The facilitator will incorporate multisensory cues, such as imagining the warmth of sunlight or the rhythmic sound of waves, to deepen the immersive experience.*Focused attention meditation*: This technique will involve sustained attention to a specific focal point, such as the breath, a mantra, or a gentle auditory cue (e.g., Tibetan singing bowl sounds). This method will be used to train cognitive flexibility, enhance concentration, and reduce mental distraction.C*Reflection and discussion (50 min)*: Following the guided meditation, while enjoying a brief reception, the participants will engage in a structured discussion to reflect on their experiences, share insights, and discuss any challenges encountered during practice. This segment will foster a sense of community and support, allowing participants to integrate meditation principles into their daily routines. Additionally, the facilitators will provide practical strategies for maintaining regular meditation practice and will answer the participants’ questions (Table 1).

**Table 1 Tab1:** Introducing thematic focus of verbal interaction in two intervention groups

Sessions	Intervention Group 1: Topics of meaningful conversation	Intervention Group 2: Topics of experience sharing
1	Intervention Group 1: Topics of meaningful conversation	Intervention Group 2: Topics of experience sharing
2	Sharing feelings and experiences from walking	Sharing experiences and feelings in meditation
3	Life experiences Participants can talk about positive and negative experiences in their life. This session helps them share their feelings and the lessons they have learned from life	Participants can talk about positive and negative experiences in their life. This session helps them share their feelings and the lessons they have learned from life and see how meditation helps them process these experiences
4	Exploring the impact of family and social relationships on quality of life. Participants can talk about their connections with family members, friends, and other community members and explore the challenges and joys of these relationships	Discussing psychological challenges and solutions
5	The impact of social activities A discussion of the importance of participating in social activities and how it impacts mental health and a sense of belonging	Analysis of advances and experiences in meditation
6	The importance of friendship Discussion on the role of friendships and social support in life. Participants can talk about close friends and the impact they have on their lives	Enhancing peace and continuing meditation practice
7	Challenges of aging Examine the challenges and problems that come with aging, including health problems, loneliness, and social changes, and self-care	Examine the impact of meditation on social interactions Examine how meditation can help improve social relationships, reduce stress in social encounters, and increase a sense of empathy and calm in relationships with others
8	Conclusion and the future A discussion about what they have learned from these sessions and a plan for the future. Participants can share their feelings and experiences about learning and positive changes	Final conclusion and exchange of views on experiences A discussion about what they have learned from these sessions and a plan for the future. Participants can share their feelings and experiences about learning and positive changes

### Control group

The control group will not receive any specific intervention during the study period. Instead, the participants will continue to receive standard care and support from their local healthcare centers. This approach will allow for a comparative analysis of the effects of the interventions by assessing differences in outcomes between the intervention and control groups. However, to ensure that control group participants also benefit from similar activities, they may be invited to participate in comparable sessions after the completion of the study. To adhere to ethical considerations and prevent feelings of disappointment or neglect in the control group, the following provisions will be considered:Provision of information and counselingMembers of the control group will receive comprehensive counseling regarding their health and well-being challenges. This counseling will include guidance on effective self-care and quality of life.Invitation to participate in future activitiesUpon completion of the main intervention, members of the control group may be invited to participate in similar activities. These activities will include educational sessions or social programs designed to promote participants’ health and awareness after the study concludes.Review and provision of resultsAt the end of the study, the overall research findings will be presented to all participants (both intervention and control groups). This action will foster a sense of involvement and value among participants and will provide them with information regarding the impact of the interventions.Creation of learning opportunitiesFollowing the intervention, educational sessions on topics related to mental and physical health in older adulthood will be organized for the control group. This will provide them with the opportunity to benefit from similar experiences, thereby upholding the ethical principles of the research in a way that ensures all participants, including members of the control group, will gain from their participation.

The following diagram will illustrate the anticipated impact of the interventions on mental health and cognitive empowerment in older adults. The walking group with meaningful conversation is expected to demonstrate greater improvements in mental vitality, whereas the meditation group is expected to show more progress in cognitive empowerment. The control group is expected to experience fewer changes (Fig. 2).

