### Hypothesis

This research is based on the premise that the type of nature-based activity will have differential effects on the cognitive empowerment and mental vitality of older adults. It is expected that walking accompanied by meaningful conversations will have a stronger impact on these outcomes through social interaction, cognitive stimulation, and the enhancement of a sense of meaning, while meditation in nature, by reducing stress, improving focus, and strengthening emotional regulation, may produce different yet significant effects. Furthermore, it is hypothesized that both interventions will lead to greater improvements in mental vitality and cognitive empowerment in older adults compared to the control group, which will not be exposed to any structured nature-based activities.

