### Study population and setting

The target population will consist of women aged 60 years and older residing in urban and rural areas of Khafr County, located in Fars Province, Iran, all of whom will be registered at urban and rural comprehensive health service centers. The inclusion criteria will be the absence of psychiatric disorders, cognitive impairment (Mini-Cog screened), balance disorders, and gait problems (tandem gait screened), willingness to participate in the study, and provision of informed consent. Individuals experiencing bereavement within the past 6 months and those missing at least one intervention session will be excluded from the study.

To maintain the integrity of the study results, participants should avoid enrolling in any formalized group activities with similar aims to the study interventions, such as scheduled walking clubs, guided meditation sessions, or therapeutic nature programs, for the duration of the 8-week intervention phase. There are no restrictions on standard medical care or informal daily routines.

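### The control arm may receive similar activities and educational sessions before the 3-month sustainability assessment, because their start is tied both to the end of the study and to the end of the intervention

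*Protocol article*

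**What the plan says.** All the timing statements for the control arm are in the Control group section of the protocol article.

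- **Tied to the end of the study.** "The control group will not receive any specific intervention during the study period". Also, "they may be invited to participate in comparable sessions after the completion of the study". The activities on offer are described as promoting "health and awareness after the study concludes".
- **Tied to the end of the intervention.** Upon "completion of the main intervention, members of the control group may be invited to participate in similar activities". And, following "the intervention, educational sessions on topics related to mental and physical health in older adulthood will be organized for the control group".
- **No timing given.** Controls "will receive comprehensive counseling regarding their health and well-being challenges".

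The list is introduced as provisions that will be considered. The activities it names are educational sessions or social programs.

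Two other places bear on the point. Study population and setting asks participants to stay out of organised activities such as "scheduled walking clubs, guided meditation sessions, or therapeutic nature programs, for the duration of the 8-week intervention phase". The Hypothesis section expects greater improvement in both active arms "compared to the control group, which will not be exposed to any structured nature-based activities".

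**The concern.** The intervention ends at about week 8, but the study continues to an assessment 3 months later. A team that follows the second set of statements could run sessions for controls inside that interval and still be within the protocol.

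Sustainability of effects is a stated aim (Aims) and a secondary outcome on both questionnaires (Secondary outcomes). The Follow-up (long-term evaluation) section uses month 3 to decide whether gains last or fade. If controls gain between week 8 and month 3, the active-versus-control difference shrinks. In that contrast, a durable effect diluted by control exposure would look the same as an effect that had worn off.

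**Working it through.** The protocol gives no figure to reproduce here. The check sets the timing statements beside the assessment schedule.

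**1. What the intervention means in this document.** Study design lists the intervention (phase 6), the post-test (phase 7) and the 3-month follow-up (phase 8) as separate phases. The Posttest section places the post-test at the end of the 8-week intervention period, and the Follow-up (long-term evaluation) section counts three months from the intervention. The word therefore normally means the 8-week phase, not the whole study. In the Control group section itself, the provision on sharing results refers to the end of the study when that is what is meant.

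**2. Order of events.**

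| Time | Event | Control-arm statements tied to it |
|---|---|---|
| About week 8 | Intervention ends, post-test | Invitation to similar activities; educational sessions |
| 3 months later | Follow-up assessment | None |
| After follow-up | Study ends | Comparable sessions; activities after the study concludes |

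The sustainability assessment lies between the two start points.

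**3. Whether another rule closes the gap.** The restriction in Study population and setting stops with the 8-week phase. No section says that control activities must wait for the 3-month visit.

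**4. Whether the content could matter.** The Control group section says the educational sessions let controls gain from experiences similar to those of the active arms. Topics overlap with Table 1, where the walking arm discusses social activities (session 5) and the health problems of ageing and self-care (session 7). Both outcomes are unblinded self-reports. The content may still be weaker than the trial interventions.

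**5. Scope.**
- Window: 3 months × (365.25 / 12) / 7 = 13.0 weeks, against an 8-week intervention phase.
- Participants who could be exposed: up to 37, the planned control arm.
- Comparisons: three arms give 3 pairwise comparisons per outcome. Statistical methods names them for week 8. If they are repeated at month 3 (an assumption), 2 of 3 involve the control and 1 (walking versus meditation) does not. None of the 3 primary week-8 comparisons is affected.

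**6. Size.** If D is the undiluted month-3 difference from control and controls gain a fraction f of it beforehand, the observed difference is D × (1 − f). The protocol gives nothing from which f could be set, so no numerical dilution is claimed.

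**The case against.** The strongest reply is that the two timings are compatible: anything held after the study is also held after the intervention, so the second set of statements gives only a lower bound. The section opens by ruling out any specific intervention during the study period, and follow-up is a phase of the study. The sentence inviting controls to similar activities is followed directly by one that places those activities after the study concludes. Educational sessions are not nature-based, so they need not contradict the Hypothesis section. The restriction on group activities governs what participants join for themselves, not what the trial team offers. The provisions are only to be considered, and the schedule figure is not shown.

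Much of this is fair. It softens the invitation sentence, and it confirms that early exposure is permitted rather than planned. It does not reach the sentence on educational sessions, which has no such qualifier, says the sessions will be organised and gives the intervention as their starting point. Set against the opening rule, that is a conflicting timing rule and not merely an omitted detail. The missing timing of the counselling is different: it is a gap, not a conflict.

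The reply is also right that the harm is limited. The change from week 8 to month 3 within each active arm bears on whether gains fade and is unaffected. The 13 weeks measure the gap between two dates, not an amount of exposure.

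**Conclusion.** The concern holds. As written, the Control group section allows control-arm activities and educational sessions in the 3 months before the sustainability assessment, while also stating that controls receive nothing specific during the study. The month-3 contrasts with control, on both questionnaires, are exposed to dilution of unknown size toward the null.

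The limits matter. These contrasts are secondary and declared exploratory. The week-8 primary outcome, walking versus meditation, and within-arm change in the active groups are not affected. Harm arises only if the sessions are delivered early and have some effect. The conclusion assumes that the intervention carries here the meaning it has elsewhere in the protocol, namely the 8-week phase. This should be corrected because it protects a stated aim at little cost; it does not threaten the main result.

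**What to change.** In the Control group section, replace both phrases that start the provisions at the end of the intervention with one rule: similar activities, educational sessions and social programs for controls begin only after the 3-month assessment is complete. Apply the same rule to any counselling beyond routine care. One calendar date is enough, because the Requirement section has all participants enter the intervention together.

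If earlier delivery is kept, record each control's attendance and describe the 3-month contrast as one against a control with delayed or lesser exposure. The same fallback serves if the trial has already begun.

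The cost is a wording change; Trial status reports that recruitment had not started at version 1.0. Controls would wait about three months longer but would still receive everything promised, which fits the section's own statement that comparable sessions follow completion of the study.

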**Fig. 2 Fig2:**
[figure not shown]
Expected impact of interventions on mental vitality and cognitive empowerment

### Follow-up

To minimize intervention attrition rates and ensure participant retention, several strategies will be implemented:*Regular follow-up*: Weekly reminder phone calls or messages will be sent to participants to notify them of upcoming sessions and to emphasize the importance of their attendance. Local healthcare staff, health ambassadors, and liaisons will also maintain regular contact with participants to reinforce their sense of commitment to the study.*Supportive and motivational environment*: Participants will be continuously reminded of the significance of their participation and the potential benefits of the study on their well-being. A social and interactive atmosphere will be fostered during the sessions to promote a sense of belonging and motivation to remain engaged throughout the study.*Family and caregiver involvement*: Family members will be encouraged to support their older adult relatives by facilitating their attendance at sessions. Caregivers will be educated on their important role in promoting consistent participation and adherence to the study protocol. These strategies will help reduce attrition, enhance participant satisfaction and engagement, and ensure the collection of valid and reliable data.Furthermore, to facilitate attendance, round-trip transportation to the session venue will be provided. All participants will receive a summary of the aggregate study findings upon completion as tokens of appreciation.

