**Fig. 1 Fig1:**
[figure not shown]
Study design algorithm: eligibility criteria, random allocation, and follow-up process

Given the active nature of the sessions, participants and those leading the groups will know their assignment. Outcome scores come directly from participant questionnaires, so those results are also unblinded. For the analysis phase, the statistician will work without knowing group labels until the final results are prepared.

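### The retention plan keeps reminding participants of the study's potential benefits, although the primary outcome is an unblinded self-report questionnaire

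*Protocol article*

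**What the plan says.** The Follow-up section of the protocol article introduces its measures with this aim: "To minimize intervention attrition rates and ensure participant retention, several strategies will be implemented". One of them is: "Participants will be continuously reminded of the significance of their participation and the potential benefits of the study on their well-being". The sentence names no arm and does not say who gives the reminder.

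The measures around it are mostly tied to sessions. The weekly contact reads: "Weekly reminder phone calls or messages will be sent to participants to notify them of upcoming sessions and to emphasize the importance of their attendance". The motivational measure reads: "A social and interactive atmosphere will be fostered during the sessions to promote a sense of belonging and motivation to remain engaged throughout the study". Relatives are asked to help with attendance, and transport to the venue is provided. One channel is not tied to sessions: "Local healthcare staff, health ambassadors, and liaisons will also maintain regular contact with participants to reinforce their sense of commitment to the study".

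On the comparator, the Control group section states: "The control group will not receive any specific intervention during the study period". It then lists standard care, counselling on health and self-care, and an offer of activities after the study.

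On blinding, the Study design section says that participants and group leaders know the assignment, and adds: "Outcome scores come directly from participant questionnaires, so those results are also unblinded". The Primary outcome section defines the endpoint as the change in the Cognitive Empowerment questionnaire score from baseline to week 8.

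**The concern.** Blinding is not feasible here, so the self-rated score at week 8 is already open to expectation. The benefit reminder adds to that exposure and is avoidable. It is a retention device, not a component of either activity, yet it repeatedly tells women that taking part may do them good before they rate themselves.

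The message matters only so far as it acts differently by arm, and there are two reasons to expect that it does. First, most of the planned contact is built around sessions, which only the walking and meditation groups have. Second, a woman who knows she is receiving an activity has something to attach the promised benefit to, while a control does not. Either would move self-ratings in the active arms relative to control whether or not the activity works. Walking versus meditation is less exposed, because both arms have sessions and the same retention contacts.

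**Working it through.** **Passages side by side**

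| Element | What the article states | Section |
|---|---|---|
| Benefit message | Continuous, arm not named | Follow-up |
| Weekly contact, session atmosphere, help from relatives, transport | Tied to sessions | Follow-up |
| Local-staff contact | Not tied to sessions, arm not named | Follow-up |
| Control condition | No sessions during the study; standard care and counselling, counselling without a schedule | Control group |
| Primary outcome | Self-report, unblinded, week 8 | Study design; Primary outcome |

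That the message falls mainly on the active arms is an inference from the session-based channels. The article does not state it.

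**Is it handled elsewhere?** The Discussion concedes that self-report may bring response bias, but says nothing of bias that differs by arm. It also credits blinding with reducing bias in outcome assessment, which conflicts with Study design. Trial oversight and auditing calls the self-reported primary outcomes objective. The article describes no neutral message and no matched contact for controls.

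**The plan's own figures, reproduced**
- Effect size (Sample size): pooled SD = sqrt((1.8² + 2.1²)/2) = 1.956; (28.3 − 27.5)/1.956 = 0.409, stated as 0.41.
- Alpha per comparison (Statistical methods): 0.05/3 = 0.0167, as stated.
- Arm size (Sample size): 111/3 = 37, as stated. After the planned 20% loss, 37 × 0.8 = 29.6.

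**Illustration.** No document gives the size of an expectancy effect. Assume no true effect, and that the reminders raise the self-rated score in an active arm by b SD against control. Use a normal approximation with individual-level variance and no allowance for clustering.

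SE = sqrt(2/n), which is 0.2325 for n = 37 and 0.2599 for n = 29.6. The critical value for two-sided 0.0167 is 2.394.

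Rejection probability = P(Z > 2.394 − b/SE) + P(Z < −2.394 − b/SE).

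For b = 0.2 and n = 37: b/SE = 0.860, so P(Z > 1.534) + P(Z < −3.254) = 0.0625 + 0.0006 = 0.0631.

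| Assumed shift b (SD) | n = 37 | n = 29.6 |
|---|---|---|
| 0 | 1.7% | 1.7% |
| 0.1 | 2.7% | 2.5% |
| 0.2 | 6.3% | 5.3% |
| 0.3 | 13.5% | 10.8% |

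For scale, 0.2/0.41 = 0.49, so a shift of 0.2 SD is about half of the planned effect.

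**The case against.** The strongest reply is that the text does not confine the message to the active arms. It speaks of participants in general and of benefits of the study rather than of an activity, and the local-staff contact could reach controls, who are also offered counselling. This stands as a limit on the claim. A reader might infer that only the active arms are reminded, but the documents do not say so. The point does not depend on it, because unblinded controls know that they receive no activity.

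A reader might also infer that controls, with fewer session-based supports, will be lost more often. The article gives no figure for loss by arm, and the local-staff contact and the control-group provisions point the other way. Unequal loss is not claimed here.

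A reader might extend the criticism to the facilitation text of the walking arm ("Positive experiences shared during the conversations will be reinforced by the researcher") and to the closing session in Table 1, where women may share positive changes. Both are content of the interventions under test, and the first concerns one arm only. Changing them would change the treatment, so they are left alone.

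Three further replies have some force. The reminder concerns general well-being, which lies closer to mental vitality, a secondary outcome, than to the primary questionnaire. Lack of blinding and response bias are disclosed, though not a difference between arms. Exact scripts may sit in a fuller document that is not shown; but the benefit message is stated in the article itself, so the criticism is of what is written, not of a missing detail.

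Finally, the shifts in the illustration are chosen values, and they credit the whole shift to the reminders. How much one sentence adds to the expectancy already present in an unblinded, no-intervention comparison is unknown.

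**Conclusion.** The concern holds in a limited form. A stated retention procedure promotes the study's potential benefits to women whose own unblinded ratings are the primary outcome. It can bias the walking-versus-control and meditation-versus-control comparisons towards benefit, and it is not needed for retention.

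The direction rests on one assumption: that a benefit message raises expectations more in women who know they have an activity, helped by contacts that are mostly session-based. The size cannot be derived from the documents. If the shift were 0.1 to 0.3 SD, the false-positive rate per comparison would be about 2.7% to 13.5% with full arms, or 2.5% to 10.8% after 20% loss, against a nominal 1.7%. These rates show sensitivity and are not an estimate of the bias in this trial. The change should be made because the source of bias is avoidable and cheap to remove.

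**What to change.** In the Follow-up section, end the quoted sentence after the part on the significance of taking part and delete the clause on benefits. In its place, set one neutral retention message for all three arms at the same weekly frequency. It should say only that every group's answers matter and give the date of the next session or, for controls, the next assessment. State expressly that the message and its schedule are the same in every arm.

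The cost is a revised reminder text and a weekly contact with 37 controls. The messages may motivate attendance slightly less. Trial status says that recruitment had not begun under this version, so the change could be made before enrolment if that is still the case. It does not remove the expectancy inherent in an unblinded comparison with no intervention, which should remain among the stated limitations as a bias that may differ by arm.
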